### Strategies to improve adherence to interventions {11c}

Protocol adherence is monitored by the authors of the study, who ensure that the manual-based intervention is conducted as intended and that all the data were collected as described. To support and enhance adherence, all interventionists undergo training to deliver the intervention, emphasizing the importance of fidelity to the manual. After each session, a session protocol is created in which any deviations from the manual or noteworthy occurrences are documented. This ongoing documentation allows for timely feedback and corrective actions if necessary, further reinforcing adherence to the intervention protocol.

### Relevant concomitant care permitted or prohibited during the trial {11d}

There is no specific concomitant care administered nor prohibited during the trial.

### Provisions for post-trial care {30}

There is no anticipated harm or compensation for trial participation.

### Outcomes {12}

Primary outcomes include severity of tobacco dependence, smoking status, and mental health symptoms. All measures will be assessed at baseline (diagnostic session; *t*_0_), post (*t*_1_; *t*_0_ + 3 weeks), at follow-up assessment 1 (*t*_2_; *t*_1_ + 6 weeks), and at follow-up 2 (*t*_3_; *t*_1_ + 6 months).

#### Primary outcomes targeting smoking behavior

Changes in tobacco dependency over time are operationalized as follows:Mean score changes in the"Fagerström Test for Nicotine Dependence"[20],German version: [9].Mean score changes in the “Alcohol, Smoking, and Substance Involvement Screening Test” (ASSIST) subscale for tobacco [58].Mean score changes in the measured carbon monoxide (CO) level in exhaled breath using the Smokerlyzer®, additionally assessed during each session of the intervention.

Changes in smoking status over time are operationalized as follows:d.Changes in the proportion of positive versus negative results in self-administered urine tests measuring cotinine content, using a dichotomous outcome (positive/negative; cutoff 200 ng/ml; for an overview, see [8]).

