## Interventions

### Explanation for the choice of comparators {6b}

By comparing the intensified smoking cessation program implemented prior to psychotherapy to a waiting control condition, we aim to evaluate the effectiveness and potential superiority of our approach regarding smoking cessation success and improvement in mental health symptoms. It is important to acknowledge that participants in both conditions may seek or receive other forms of psychotherapeutic treatment during the post- and 6-month follow-up assessments. To account for this, we will inquire about any additional treatments participants may have undergone and control for these variables in our analysis. Specifically, all additional treatments will be systematically documented and coded as categorical variables (e.g., concurrent individual psychotherapy, group therapy, psychopharmacological treatment). Dummy variables representing the presence or absence of each treatment type will be included as covariates in the repeated-measures ANOVAs. This approach not only ensures a more accurate comparison but also reflects the naturalistic conditions under which the study is conducted.

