#### Primary outcome instruments targeting biomarkers

Carbon monoxide is assessed using a piCO™ Smokerlyzer® (Bedfont Scientific Ltd.). CO levels are objective markers of heavy smoking, and a value of 7.5 ppm in exhaled CO can be considered an appropriate cutoff to differentiate non-smokers from active smokers [2]. Cotinine is assessed using single rapid urine tests (nal von minden gmbH) with a cutoff of 200 ng/mL, which is a commonly used cutoff for detecting nicotine exposure for up to 5 days [34].

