### Interim analyses {21b}

No interim analyses or formal stopping rules are planned for this study. The decision is based on the low-risk nature of the intervention, which involves behavioral support without invasive procedures or pharmacological treatments. Additionally, given the naturalistic design, we decided not to conduct interim analyses as they might compromise the integrity of the final data analysis. However, we remain attentive to participant safety and feedback. If any adverse events are reported or significant concerns are raised during participant evaluations (as part of Patient and Public Involvement), appropriate steps, including potential study termination, will be considered and documented accordingly.

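### Smoking status is defined only by urine cotinine while no nicotine product is prohibited, so a cigarette quitter whose product use keeps cotinine at or above the cutoff is counted as a smoker

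*Protocol article*

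**What the plan says.** All of this is in the protocol article.

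- **Outcome.** Outcomes {12} makes smoking status a primary outcome. The section on primary outcomes targeting smoking behavior gives it one operationalization: "Changes in the proportion of positive versus negative results in self-administered urine tests measuring cotinine content", "using a dichotomous outcome (positive/negative; cutoff 200 ng/ml".
- **What the test detects.** The section on biomarker instruments describes the 200 ng/mL threshold as one "which is a commonly used cutoff for detecting nicotine exposure for up to 5 days".
- **Exhaled CO.** The same section states that "a value of 7.5 ppm in exhaled CO can be considered an appropriate cutoff to differentiate non-smokers from active smokers". As an outcome, however, CO appears only under tobacco dependency, as a continuous change: "Mean score changes in the measured carbon monoxide (CO) level in exhaled breath using the Smokerlyzer".
- **Concomitant care {11d}.** "There is no specific concomitant care administered nor prohibited during the trial".
- **The programme.** Interim analyses {21b} describes it as one "which involves behavioral support without invasive procedures or pharmacological treatments". Any nicotine product would therefore come from outside the intervention.
- **Additional treatments.** Under the choice of comparators {6b} they are documented and coded, and then: "Dummy variables representing the presence or absence of each treatment type will be included as covariates in the repeated-measures ANOVAs".
- **Test.** Statistical methods {20a} compares abstinence rates at post-treatment and follow-up by chi-squared tests. It gives no further definition of abstinence.

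**The concern.** The outcome is named after smoking, but the marker responds to nicotine. The two come apart for a patient who has given up cigarettes and takes nicotine in another form. Nothing in the article rules such use out, and its background section lists pharmacological treatments among the guideline options for this population. No rule says how such a patient is classified, so the stated definition applies by default and returns a smoker.

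The error runs one way: it removes true quitters from the abstinent count and adds none. If it removes more of them, in absolute terms, from the arm with more quitters, the observed difference in abstinence is too small. A real effect could then be reported as absent, in a trial whose size was not set for this comparison.

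**Working it through.** **Inputs from the protocol article**
- 31 participants per arm, α = 0.05 (Sample size {14}).
- Cotinine cutoff 200 ng/ml; CO cutoff 7.5 ppm.
- A 2:1 ratio of abstinence rates from the cited trial of the app (Intervention description {11a}), used only to illustrate the arm split.

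**Inputs assumed, because the documents give none**
- True quit rates of 30% (experimental) and 10% (control).
- u, the share of true quitters who use a nicotine product *and* reach the cutoff, varied from 0 to 0.50.
- No other error in the test.

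**The plan's own figure.** The total of 62 is for the 2 × 4 ANOVA. It reproduces with f = 0.25 (assumed for a moderate effect) and noncentrality f²(N − 2)(m − 1) = 0.0625 × 60 × 3 = 11.25 on 3 and 180 degrees of freedom, giving power 0.804. There is no sample size calculation for the abstinence comparison, so nothing is available to reproduce there.

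**Step 1: effect on the difference.** The observed abstinence rate in an arm is q(1 − u). With the same u in both arms the observed difference is (q_T − q_C)(1 − u). The ratio of the two rates does not change. Power is the two-sided normal approximation with 31 per arm.

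| Scenario | Observed rates | Difference | Power |
|---|---|---|---|
| u = 0 | 30% vs 10% | 20 points | 0.50 |
| u = 0.20, both arms | 24% vs 8% | 16 points | 0.40 |
| u = 0.25, both arms | 22.5% vs 7.5% | 15 points | 0.38 |
| u = 0.50, both arms | 15% vs 5% | 10 points | 0.26 |
| u = 0.20, experimental arm only | 24% vs 10% | 14 points | 0.31 |
| u = 0.50, experimental arm only | 15% vs 10% | 5 points | 0.09 |

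The last two rows are the extreme case, with no misclassified quitter in the control arm.

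**Step 2: where the misclassified quitters are.** The experimental arm holds the share q_T·u_T / (q_T·u_T + q_C·u_C). With equal u this depends only on the quit rates: 2/3 = 67% at 2:1 and 3/4 = 75% at 3:1. At 2:1 the split is even if control quitters are misclassified twice as often as experimental ones.

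**Step 3: direction.** The difference loses q_T·u_T − q_C·u_C. At 30% versus 10% that loss is zero when u_C = 3u_T and turns into a gain only beyond it. Below that point the bias is towards no effect.

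**Step 4: do the planned safeguards help?** The treatment dummies belong to the ANOVAs, and a chi-squared test carries no covariates. Adjustment would not repair a misclassified outcome in any case. The CO cutoff could separate smoking from other nicotine intake, but no stated outcome uses it to decide status.

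**The case against.** Several points on the other side carry weight.

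- **The arm split.** A reader might infer that the misclassified patients are mostly in the experimental arm. The documents do not establish this. They report no product use in either arm, and the programme supplies no pharmacological treatment. Controls wait six months, and the discussion says that participants must show an interest in changing their smoking, so controls may try products themselves. The inference needs more quitters in the experimental arm and broadly similar use among quitters in both.
- **The size.** For the same reason, a fall to between 14 and 5 points describes only the case in which all users are in the experimental arm.
- **Not every user.** A reader might take every product user to be scored positive. That holds only if cotinine reaches 200 ng/ml, and the documents do not say what levels such products produce.
- **What is recorded.** Nicotine replacement and e-cigarettes are named nowhere, but the list of additional treatments is given as examples, so product use may be recorded. This stands, though recording it for the ANOVAs does not settle the classification.
- **The abstinence measure.** The statistical section does not name it, and a full protocol or analysis plan may bring in CO. Even so, the article states a definition of smoking status, and cotinine is the only measure in it.
- **Nicotine as the target.** Much of the rationale concerns nicotine itself, so a nicotine-free endpoint would be coherent. It would then need that name, since the article calls it smoking status.
- **Limited reach.** Cotinine is one of eight primary measures. CO, the FTND and the ASSIST tobacco scale also bear on smoking, so the trial's conclusion does not rest on this outcome alone.

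**Conclusion.** The point holds as a mismatch between the named outcome and its stated measure. Under the rule as written, a cigarette-abstinent patient whose nicotine-product use brings cotinine to the cutoff counts as a smoker, and nothing planned corrects this in the abstinence tests.

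With equal misclassification in both arms, an assumed 20-point difference becomes 16 points at u = 0.20 and 10 at u = 0.50. Power on 31 per arm goes from about 0.50 to 0.40 and 0.26. These figures rest on assumed quit rates and an assumed u. If few patients use such products, or few users reach the cutoff, the effect is small. A heavier concentration in the experimental arm is plausible under the trial's own hypothesis but is not documented.

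This is worth correcting because it concerns a primary outcome and the remedy is cheap. It does not invalidate the other smoking measures.

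**What to change.** 1. At every assessment, in both arms, ask whether any nicotine product was used in the past 5 days, which is the window the article gives for the test.
2. Define abstinence for reported users as self-reported non-smoking plus exhaled CO below the article's 7.5 ppm cutoff, and for non-users as a negative cotinine test. State that the chi-squared tests use this definition.
3. Report two sensitivity analyses: (a) self-reported non-smoking plus CO below 7.5 ppm applied uniformly to all participants, and (b) cotinine alone.

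**Cost.** One question per visit and a few sentences in the outcome definition. CO is already measured at all four assessments, so no device or visit is added. Data collection began in August 2024 and runs to April 2027, so the question can still be added for remaining visits. The report should say how visits already held were classified.

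**Downside.** CO may miss light or less recent smoking, so the criterion for users is the laxer one. In an unblinded trial that could favour whichever arm has more users. Analysis (a), with one rule for everyone, guards against this.

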#### Primary outcomes targeting mental health symptoms

Changes in mental health symptoms related to mental disorders are measured by self-report questionnaires, which will also be assessed at the four measurement points mentioned above (baseline, post, follow-up 1 and 2). The questionnaires target general psychological well-being and perceived quality of life, symptoms associated with mental disorders, and depressive symptoms.

Changes in mental health status over time are operationalized as follows:Mean score changes in the German version of the “WHO-5 Well-being Index” ([WHO-5]; [52]).Mean score changes in the German version of the “WHO Quality of Life-BREF” ([WHOQOL-BREF]; [1]).Mean score changes in the “Brief Symptom Check List” ([BSCL]; [23])Mean score changes in the “Beck Depression Inventory-Revised” ([BDI-ll]; [6]).

#### Secondary and exploratory analyses

Secondary and exploratory analyses will investigate the impact of the treatment on other clinically relevant factors, such as implicit processes associated with smoking, alongside examining potential moderators or mediators, such as both global and smoking-related self-efficacy, both global motivation to change and specific motivation to quit smoking, and attitudes towards online interventions. All secondary variables will be assessed at all measurement points (baseline, post, follow-up1 and 2), with the exception of attitudes towards online interventions, which will only be assessed at baseline.

##### Implicit processes

Changes in implicit processes associated with smoking over time are operationalized as follows:Mean score changes in the nicotine-related approach biases as assessed with the Approach-Avoidance Task [53] adapted for smoking [42].

##### Self-efficacy

To capture a comprehensive view of self-efficacy, self-efficacy is assessed by two questionnaires. This dual approach ensures that both broad and behavior-specific aspects of self-efficacy are captured. We will examine changes in both general and smoking-related self-efficacy as potential moderating or mediating factors of the treatment effect, as well as secondary outcome variables.

Changes in both general and smoking-related self-efficacy are operationalized as follows:b.Mean score changes in the German version of the “Generalized Self-Efficacy Scale” ([GSE]; [33]).c.Mean score changes in the German version of the “Self-Efficacy Scale for Smoking” ([SESS]; [32]).

##### Motivation

Changes in patients’ motivation to change will be assessed using multiple questionnaires to provide a detailed view of their readiness for change, stage of behavioral change, and specific motivation to quit smoking. By employing a range of measures, we aim to capture various dimensions of motivation and how they evolve throughout the intervention. This approach will allow us to analyze changes in motivation as potential moderating or mediating factors in the treatment effect, and to better understand the role of motivation in the overall effectiveness of the smoking cessation program.

Changes in patients’ motivation are operation as follows:d.Mean score changes in the German version of the “University of Rhode Island Change Assessment Scale” ([FEVER]; [26]).e.Mean score changes in the “Scale for Stages of Change” ([SOC]; [18]).f.Mean score changes in the “Motivation to Stop Scale” ([MTSS]; [49]).

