**Methods:**

A single-center randomized controlled trial in an outpatient psychotherapeutic clinic will examine the effects of an intensified smoking cessation intervention versus a waiting control condition. The primary outcome measures include smokers’ nicotine dependence, smoking behavior, and mental health symptoms related to their primary mental disorder, analyzed using variance analysis methods. The smoking intervention consists of a common guideline-based cognitive-behavioral program supplemented by a digital health application. Secondary outcomes include changes in self-reported self-efficacy and implicit cognitive biases. In addition, motivational measures, self-efficacy, implicit approach tendencies, and attitudes toward online interventions will be assessed as secondary measures and examined as potential predictors, moderators, or mediators in exploratory analyses. Attitudes toward online interventions will be measured once at baseline, while all other measures will be assessed before the intervention, post-treatment, and at 6-week and 6-month follow-up sessions.

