### Intervention description {11a}

The intervention for the experimental group consists of a manual-based six-step smoking cessation program, adapted from the widely implemented and continuously evaluated smoking cessation program developed by the *Arbeitskreis Tabakentwöhnung* (Smoking Cessation Working Group) at the University Hospital for Psychiatry and Psychotherapy in Tübingen. This program, detailed in the manual by Batra and Buchkremer [3] and recently updated [4], is rooted in cognitive–behavioral therapy (CBT) and designed for both group and individual settings, though this study will utilize the individual setting. The program spans six sessions, during which participants will receive guidance on preparing for and executing their smoking cessation efforts, developing strategies to maintain abstinence, and preventing relapse. The sessions are organized into three distinct phases, as outlined in Table 1.

**Table 1 Tab1:** Smoking intervention phases in the intervention group

Phase 1	Session 1	Abstinence preparation phase: Focuses on motivating individuals and understanding their smoking habits
	Session 2	
Phase 2	Session 3	Cessation phase: Provides specific strategies for quitting smoking and managing cravings
	Session 4	
Phase 3	Session 5	Stabilization phase: Emphasizes building alternative behaviors, coping with potential relapse triggers, promoting overall health, and managing relapses
	Session 6	

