### Participant timeline {13}

Smoking patients who have had three psychotherapeutic consultations at the Psychotherapeutic Outpatient Center of the University of Siegen will be informed about the option of participation in the current study. Interested participants will be contacted by the study team and undergo a telephone interview to determine eligibility and fulfillment of the inclusion criteria (*− t*_1_). Following telephone screening for a duration of 10–30 min, patients will be invited to the first smoking cessation session, during which informed consent will be obtained and psychological symptoms will be assessed within the course of a diagnostic session (baseline, *t*_*0*_). After the diagnostic session, during which all baseline measures will be assessed, patients will be randomly assigned either to the experimental group or the passive control group. The experimental condition will receive a 6-step smoking cessation program and additional access to a smartphone-based self-help application. The duration of the intervention will be three weeks. Afterwards, patients will be invited again to assess all measures of interest (*t*_1_). Six weeks (*t*_2_) and 6 months (*t*_3_) after completion, patients will be invited once again for follow-up assessments. The participants’ timelines and data assessment points are shown in Table 2..

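### Changes in motivation and self-efficacy, observed after randomisation and targeted by the treatment, are named as possible moderators; this can produce false moderation, and moderation should use baseline values only

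*Protocol article*

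**What the plan says.** The protocol article names the moderator variables in two subsections of Secondary and exploratory analyses. Under Self-efficacy: "We will examine changes in both general and smoking-related self-efficacy as potential moderating or mediating factors of the treatment effect". Under Motivation: "This approach will allow us to analyze changes in motivation as potential moderating or mediating factors in the treatment effect". Both then define the variables as mean score changes (GSE and SESS; FEVER, SOC and MTSS). The self-efficacy changes are also listed as secondary outcomes.

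Four other places fix the timing and status:

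- Participant timeline {13}: "After the diagnostic session, during which all baseline measures will be assessed, patients will be randomly assigned". Every assessment from t1 on is therefore post-randomisation.
- The Motivation section is interested in the dimensions of motivation and "how they evolve throughout the intervention".
- Table 1 in Intervention description {11a} says of the first treatment phase: "Focuses on motivating individuals and understanding their smoking habits".
- The abstract says that these measures will be "examined as potential predictors, moderators, or mediators in exploratory analyses".

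The scales are collected at t0 as well as at t1 to t3. Only the attitude questionnaire (APOI) is restricted to baseline. Statistical methods {20a} names regression or structural equation modelling for mediators and gives no model for moderators.

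**The concern.** A moderator should be something the treatment cannot alter, so that the two arms remain comparable at each of its values. A change in motivation or self-efficacy fails this test, because the programme is built to alter it. Patients whose motivation rose during six therapy sessions are not the counterparts of patients whose motivation rose on a waiting list. A group-by-change term then mixes three things: true effect modification, the treatment's effect on the change, and any cause that the change shares with the outcome.

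Two results are at stake. The interaction test may declare a moderator where none exists, and the treatment effect at a given value of the change may be distorted. The Discussion gives as an example for future studies the possible need for enough self-efficacy before the first session. That question concerns baseline values, and moderation by change does not answer it.

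**Working it through.** **The plan's own figure.** The only design figure is 62 patients, 31 per arm, for the 2 × 4 mixed ANOVA at α = 0.05 and power 0.80 (Sample size {14}). The effect is called moderate without a number. Assume f = 0.25 and noncentrality λ = f²(N − 2)(m − 1) with m = 4 times. N = 62 gives λ = 0.0625 × 60 × 3 = 11.25 on 3 and 180 degrees of freedom, power 0.804. N = 60 gives λ = 10.875, power 0.789. So 62 is reproduced under this option. There is no figure for the moderator analyses.

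**Simulation set-up.** From the protocol: N = 62, 1:1 allocation, α = 0.05. Everything else is assumed. A is the arm, U an unmeasured patient trait, and e and e₂ independent standard normal noise. The outcome is Y = 0.50A + 0.7U + 0.7e₂, so the effect is 0.50 for every patient. The within-arm variance is 0.49 + 0.49 = 0.98, so 0.50 is about half an SD. M is the change score and has no effect on Y. The fitted model is Y on A, M (centred) and A × M, with 4,000 trials per scenario.

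| Scenario | Assumed change M | A × M rejected | Effect at mean M |
|---|---|---|---|
| (a) No shared cause | 0.5A + e | 4.6% | 0.50 |
| (b) Shared cause, same slope and spread | 0.5A + 0.7U + 0.7e | 4.7% | 0.25 |
| (c) Shared cause acts more in treated arm | 0.5A + (0.1 + 0.7A)U + 0.7e | 22.9% | 0.34 |
| (d) Wider spread in treated arm | 0.5A + 0.7U + (0.3 + 0.7A)e | 56.3% | 0.21 |
| (e) Ceiling on the score | min(1.0A + 0.7U + 0.7e, 1.0) | 8.2% | 0.05 |
| (f) Outcome feeds back in treated arm | 0.5A + 0.6AY + 0.8e | 58.8% | 0.27 |

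**Checks by hand.** The slope of Y on M within an arm is cov(M, Y)/var(M).

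- (b): slope 0.49/0.98 = 0.50 in both arms, so there is no false interaction. The effect is 0.50 − 0.50 × 0.5 = 0.25.
- (c): slope 0.07/0.50 = 0.14 in controls and 0.56/1.13 = 0.496 in treated, a false interaction of 0.356 (simulated 0.352). The overall mean of M is 0.25, so the effect there is (0.50 − 0.496 × 0.25) − 0.14 × 0.25 = 0.376 − 0.035 = 0.341.
- (d): slopes 0.49/0.58 = 0.845 and 0.49/1.49 = 0.329, difference −0.516 (simulated −0.513).
- (f): slopes 0 and 0.588/0.9928 = 0.592 (simulated 0.593).
- (e): the assumed shift is 1.0, not 0.5. Without the ceiling the effect would be 0.50 − 0.50 × 1.0 = 0, so the 0.05 mainly reflects the larger shift, while the excess rejection comes from the ceiling.

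A larger trial is no cure. At N = 20,000, all 20 runs rejected in each of (c) to (f), and none in (b).

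**Baseline moderator, same data.** With a prognostic baseline covariate (U + 0.5B, B being independent noise) in place of M, the rejection rates were 4.6, 4.4, 5.0, 4.7, 5.7 and 6.0%. Y is generated identically in all scenarios, so these are replicates with mean 30.4/6 = 5.1%. The estimated effect was 0.49 to 0.50.

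**The case against.** The best defence is that two sentences run two ideas together: baseline values as moderators, changes as mediators. The abstract and the opening of Secondary and exploratory analyses name the measures without speaking of changes as moderators, and the Discussion's example points to baseline. This is a fair guess at the intention. However, no section restricts moderation to t0, and the two sections that define the variables give both roles to the changes.

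Four further points stand in part or in full:

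- The article gives no moderator model and may leave it to a fuller document. That absence is not criticised here; the point concerns the variable it does name.
- A group-by-change term is legitimate inside a mediation analysis, as an exposure-mediator interaction. The fix keeps it.
- Shrinkage of the conditional effect is not specific to moderation. It appears in scenario (b) without any false interaction, and a mediation model that omits the shared cause would show it too.
- The high rejection rates follow from assumed differences between arms. The documents supply no such parameters. The SOC is bounded from 0 to 4 and ends at maintenance, so a ceiling, or feedback from stopping smoking, is plausible but not shown.

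A reader might infer that false moderation must follow. Scenarios (a) and (b) show that it need not. A reader might also infer that the error reaches the primary estimates, because Methods for additional analyses {20b} allows re-evaluation for confounding. That section does not name these change scores, and the primary ANOVAs in Statistical methods {20a} do not include them. Nor does the Discussion base practice advice on a moderator test: its self-efficacy example is tied to mechanisms of possible interest to future studies.

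**Conclusion.** The concern holds in a limited form. As written, the plan would let changes that follow randomisation, and that the intervention targets, serve as moderators. False moderation arises when the change-outcome relation or the spread differs by arm, when the score has a ceiling, or when the outcome feeds back on motivation. The re-derived rejection rates run from 4.6% to 58.8% at a nominal 5%. Separately, in the scenarios where change and outcome are linked, the conditional effect falls from 0.50 to between 0.05 and 0.34. These figures show what can happen under assumed inputs; they do not forecast this trial. The analyses are exploratory, and neither the primary analysis nor the sample size of 62 is touched. The point is still worth correcting, because the valid alternative uses data already being collected.

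**What to change.** In the Self-efficacy and Motivation sections, state that moderation is tested only with the t0 values of GSE, SESS, FEVER, SOC and MTSS, through a group-by-baseline term. State also that changes in these scales are analysed only as secondary outcomes or mediators, and that a mediation model may include a group-by-mediator term.

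The cost is about one sentence in each section. No new data, visits or patients are needed, and the primary analysis stays as it is. The APOI needs no change, since it is already measured only at baseline. The approach-bias task is not called a moderator in the section that defines it, so it is left alone.
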